#### *Choice of chemotherapy regimen*

The combination of cisplatin and etoposide (PE) is the standard chemotherapy treatment in this group of patients. The use of PE is supported by 2 reviews: firstly a large systematic review of 7173 randomised patients which found that the inclusion of either cisplatin (22 trials) or etoposide (37 trials) in a chemotherapy regimen was associated with a significant survival improvement, as was the inclusion of both drugs compared to chemotherapy regimens with neither (18), and secondly a meta-analysis of 19 trials of 4054 patients which confirmed an increased survival with the inclusion of platinum of 2.6% and 4.4% at six months and one year respectively (19), and also, in a subset analysis of nine trials, showed a similar survival benefit for the inclusion of etoposide. A subsequent randomised trial of PE vs epirubicin, cyclophosphamide and vincristine in 440 patients supported this conclusion by showing that PE resulted in a better survival (20). Attempts to improve on this combination have met with limited success (21-23). The combination of Etoposide and Cisplatin has become in recent years the treatment of choice as it can be used concurrently at full doses with radiation therapy with acceptable toxicity (1,3,7). It is also simple to use in ambulatory patients.

The Canadian small cell lung cancer guidelines published in 2004 (24) are based on a systematic review and give a range of recommended regimens for concurrent chemo-radiotherapy, including cisplatin 25mg/m^2 days 1-3 or 75 mg/m^2 d1 with etoposide 100mg/m^2 d1-3. There is no good evidence for higher doses of etoposide which result in an increased risk of haematological toxicity, the use of GCSF, and dose delays. The guidelines state that there is insufficient evidence to comment on whether 4 cycles are the same as 6, whether oral is equivalent to iv etoposide, or whether carboplatin can be substituted for cisplatin. Therefore there is a strong rationale for using 4-6 cycles of cisplatin 25mg/m^2 d1-3 (or cisplatin 75mg/m^2) and etoposide 100mg/m^2 d1-3.

#### *Choice of radiotherapy regimen*

- BD regimen

Commencing radiotherapy on day 1 of chemotherapy is not feasible as the process of CT planning, volume contouring, treatment optimisation, and set-up checking takes 1-2 weeks. Hence the most feasible BD regimen would be 4-6 cycles of cisplatin 25 mg/m^2 d1-3 or 75 mg/m^2 d1 and etoposide 100 mg/m^2 d1-3, q3w with 45Gy in 30 fractions over 3 weeks commencing on day 1 of cycle 2 of chemotherapy. This would differ from the BD regimen in the Turrisi trial in that the cisplatin dose would be increased (25mg/m^2 d1-3 or 75 mg/m^2 d1 rather than 60mg/m^2 d1), the etoposide dose would be decreased (100mg/m^2 d1-3 rather than 120 mg/m^2 d1-3), and radiotherapy would start with cycle 2 rather than cycle 1.

- High dose OD regimen

A schedule of 66Gy in 33 daily fractions over 6.5 weeks has been piloted successfully with good compliance and toxicity profile (presented as a poster at the BTOG meeting in Dublin 2005) and is the subject of an existing single centre phase II study in Manchester.

## 2.0 TRIAL DESIGN

---

### 2.1 TRIAL OBJECTIVES

#### Primary end-point

- Overall survival

#### Secondary end points

- Local progression-free survival
- Metastasis-free survival
- CTCAE v3.0 toxicity
- Chemotherapy dose intensity
- Radiotherapy dose intensity

### 2.2 OVERALL DESIGN

This is a multicentre randomised phase III trial.

Patients are randomised to one of two treatment arms with 1:1 randomisation:

#### A 2-arm randomised trial comparing:

- 45Gy in 30 fractions BD radiotherapy schedule (given concurrently with cisplatin/etoposide)
- 66Gy in 33 fractions OD radiotherapy schedule (given concurrently with cisplatin/etoposide)

### 2.3 RELATED SUB-STUDIES

- **Correlative molecular studies for the CONVERT trial**

Progress in treatment of SCLC has been hampered by limited understanding of the molecular biology of this disease. It is usually diagnosed on a small biopsy specimen or fine needle aspirate insufficient for detailed molecular studies. Consequently, existing SCLC tumour banks include relatively small series (<100 patients) of samples collected over many years from patients who are heterogeneous with respect to stage and treatment received. The CONVERT trial provides a potentially unique opportunity to prospectively collect a large number of biospecimens from patients of uniform (limited) stage, who are exposed to the same chemotherapy, treated with one of two radiotherapy schedules, and for whom there will be robust clinical outcome data. Although it will still be problematic to obtain large tumour biopsy specimens for many patients, advances in genomic and proteomic technology will enable studies to be performed on blood/serum samples in addition to small biopsy specimens.

- **Biospecimens to be collected**

All patients will be asked to consent for collection of tumour samples (paraffin embedded) and blood samples as part of the trial. Blood samples (for genomic and proteomic analysis) will be collected at three timepoints: at baseline prior to any treatment, on day 22 of treatment and on completion of treatment.

- **Molecular studies to be performed**

The objectives of the molecular studies will be to gain improved insight into the molecular biology of SCLC, discover and/or validate candidate biomarkers for response, resistance or toxicity of treatment, and identify novel treatment targets for therapeutic control. The latter is a major objective since the treatments to be evaluated in this trial are anticipated to result in 55% 2 year survival at best. The specific correlative studies have yet to be defined but we anticipate that studies will employ a range of techniques including immunohistochemistry, proteomic profiling (blood/serum) and genetic studies on host and tumour DNA. It is unlikely that there will be sufficient tissue available (and no fresh frozen tissue) for gene expression profiling by cDNA or oligonucleotide microarray. Given that this biobank will be a unique resource the molecular analyses will be conducted where possible taking into account preliminary data and hypotheses generated from studies in SCLC cell lines and xenografts, and from current studies in large patient populations that aim to evaluate host genomic biomarkers of radiation toxicity or cancer predisposition. Samples will be collected globally then stored and analysed in the UK.

### **3.0 TRIAL ENTRY**

---

#### **3.1 CENTRE ELIGIBILITY**

All participating centres must:

- a) operate a formal system of Quality Assurance in Radiotherapy (QART), appendix 9.
- b) confirm that the initial stage of the radiotherapy quality assurance exercise has been successfully conducted (appendix 10) and that the CONVERT QA questionnaire was completed
- c) have conformal radiotherapy planning facilities (defined as multislice CT scanning planning on maximum 5 mm slices, customized blocking, DVH calculations for target and organs at risk, portal image verification) and a radiotherapy verification protocol
- d) have discussed suitable patients in a Multi-Disciplinary Meeting, including a clinician with a special interest in lung cancer
- e) have a formal protocol for neutropenic sepsis

A centre agreement and checklist must be completed by each centre, to ensure that they are able to comply with the protocol and data collection requirements, prior to site-specific assessment.

#### **3.2 CENTRE ENTRY CRITERIA**

##### **3.2.1 Centre Accreditation**

The following documentation must be received at the Christie Hospital Clinical Trials Unit in order for an institution to become an approved CONVERT institution:

- Confirmation that the initial stage of the radiotherapy Quality Assurance (QA) exercise has been successfully completed (See Section 3.1)
- Confirmation of favourable local research ethics committee site-specific assessment (SSA)
- A copy of the most recent version of the patient information sheet (appendix 11) and consent form (appendix 12) on local headed paper
- Signed memorandum of understanding (signed by the institution PI)
- Completed Delegation Log (signature list and delegation of responsibilities, appendix 14)
- Full contact details for all site personnel (appendix 13)

Once all of this documentation has been received, confirmation of institution approval will be sent to the Principal Investigator at each institution by the trial team at the Christie Hospital Clinical Trials Unit.

### **3.3 PATIENT ENTRY**

#### **3.3.1 Pre- randomisation evaluation**

- a) History and examination.
- b) Assessment of performance status and dyspnoea score (appendix 1 and 3)
- c) Contrasted CT scan of the thorax and upper abdomen (within 4 weeks prior to randomisation)
- d) Contrast-enhanced CT (or MRI) scan brain (within 4 weeks prior to randomisation)
- e) Pleural aspiration and cytology if possible if patient presents with a pleural effusion
- f) Pulmonary function tests [FVC, FEV1, KCO and DLCO/VA]
- g) FBC and serum biochemistry including LDH.
- h) Assessment of renal function (see appendix 5)
- i) ECG
- j) Bone scan need only be performed if there is a specific clinical indication
- k) Pregnancy test (if applicable)
- l) PET scan or PET-CT, if available. Centres who decide to use PET scans for staging will have to continue doing so for all patients entered in the trial.

#### **3.3.2 Inclusion/exclusion criteria**

Queries about eligibility criteria should be addressed prior to randomisation. Patients are eligible for the trial if all of the following criteria are met:

- a) Either sex, age  $\geq 18$  years
- b) Performance status ECOG grade 0-1 (appendix 1). Patients with PS 2 whose general condition is explained by obstructive/bulky disease likely to improve after the first cycle of chemotherapy can be included at the discretion of the local investigator. Patients with PS 2 as a result of comorbid conditions will be excluded.
- c) Histologically or cytologically confirmed SCLC
- d) No patients with mixed small-cell and non-small-cell histologic features
- e) No history of previous malignancy in the last 5 years (except non melanomatous skin or in-situ cervix carcinoma). Patients with previous malignancies (except breast cancer) and in remission for at least 5 years can be included.
- f) Limited stage disease (Veterans Administration Lung Cancer Study Group) ie patients whose disease can be encompassed within a radical radiation portal.
- g) No pleural or pericardial effusions proven to be malignant
- h) RT target volume acceptable by the local radiotherapist
- i) Pulmonary function
  - a. FEV1  $> 1$  litre or 40% predicted value
  - b. KCO (DLCO/VA)  $> 40\%$  predicted
- j) Maximum of one of the following adverse biochemical factors:
  - a. Serum alkaline phosphatase more than  $> 1.5$  times the upper limit of normal (ULN)
  - b. Serum sodium  $<$  Lower limit of Normal
  - c. Serum LDH  $>$  ULN

- k) Normal serum creatinine and calculated creatinine clearance  $\geq 50$  ml/min. If calculated creatinine clearance is  $<50$  ml/mn according to the Cockcroft and Gault formula (appendix 5), an EDTA clearance should be performed
- l) Adequate haematological function
  - a. Neutrophils  $>1.5 \times 10^9/l$
  - b. Platelets  $>100 \times 10^9/l$
- m) Adequate liver function: ALT & AST  $\leq 2.5 \times$  ULN
- n) No other previous or concomitant illness or treatment which in the opinion of the clinician will interfere with the trial treatments or comparisons
- o) No prior surgical resection of the primary tumour, no prior radiotherapy for lung cancer
- p) Considered fit to receive any of the trial regimens
- q) Female patients must satisfy the investigator that they are not pregnant, or are not of child-bearing potential, or are using adequate contraception. Men must also use adequate contraception, as etoposide is clastogenic.
- r) Patients must not be breastfeeding
- s) Patient has read the patient information sheet and has signed the consent form.
- t) Patients available for follow-up

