### 5.1 DEFINITIONS

**Adverse Event (AE):** any untoward medical occurrence in a patient or clinical trial subject administered a medicinal product and which does not necessarily have a causal relationship with this treatment. *An AE can therefore be any unfavourable and unintended sign (including an abnormal laboratory finding), symptom, or disease temporally associated with the use of an investigational medicinal product (IMP), whether or not considered related to the IMP.*

**Adverse Reaction (AR):** all untoward and unintended responses to an IMP related to any dose administered. *All AE's judged by either the reporting investigator or the sponsor as having reasonable causal relationship to a medicinal product qualify as adverse reactions. The expression reasonable causal relationship means to convey in general that there is evidence or argument to suggest a causal relationship.*

**Unexpected Adverse Reaction:** an AR, the nature and severity of which is not consistent with the applicable product information (i.e. summary of product characteristics (SmPC) for cisplatin and etoposide which are authorised products). *When the outcome of the adverse reaction is not consistent with the applicable product information this adverse reaction should be considered as unexpected. Side effects documented in the SmPC, which occur in a more severe form than anticipated, are also considered to be unexpected.*

**Serious Adverse Event (SAE):** for this trial an Adverse Event will be considered serious and require expedited reporting if it:

- results in **death** (within 30 days of last dose of chemotherapy or radiotherapy, irrespective of causality)
- is **life-threatening\*** (and is considered related to study treatment)
- requires **hospitalisation\*\***, or prolongation of existing hospitalisation (and is considered related to study treatment).
- results in persistent or significant **disability or incapacity**, (and is considered related to study treatment)
- is a **congenital anomaly or birth defect**

In addition the following will also be considered serious adverse events:

- **grade 3 and 4 radiation oesophagitis**
- **grade 3 and 4 radiation pneumonitis**

**SERIOUS ADVERSE EVENTS REQUIRE REPORTING TO THE CHIEF INVESTIGATOR WITHIN 24 HOURS, SEE SECTION 5.3 FOR FURTHER INFORMATION ON REPORTING PROCEDURES.**

Please note the following additional guidance with relation to definition of serious adverse events:

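### Eligibility criterion q joins its three conditions for women with 'or', so read literally it admits a fertile woman using no contraception, at odds with the sentence that follows it

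*Supplement*

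**What the plan says.** Section 3.3.2 of the latest protocol opens its list with "Patients are eligible for the trial if all of the following criteria are met", so every lettered item must be satisfied. Item q has two sentences. The one for women is: "Female patients must satisfy the investigator that they are not pregnant, or are not of child-bearing potential, or are using adequate contraception". The one for men is: "Men must also use adequate contraception, as etoposide is clastogenic".

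Three other places touch on the subject:

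- Section 3.3.1, item k, lists a pregnancy test before randomisation, qualified as applicable and with no time window.
- The visit table in Section 6.4 has no pregnancy-test row, either at screening or during treatment.
- Section 5.1 counts a "congenital anomaly or birth defect" as a serious adverse event. That is a reporting rule and not a preventive one.

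**The concern.** Item q protects against exposing a pregnancy to the trial treatment. The reason it gives, that etoposide is clastogenic, applies to men and women alike, since both receive the drug. Yet the sentence for men is an unconditional requirement, while the sentence for women makes contraception only one of three sufficient conditions.

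Not being pregnant describes a woman's state when she is assessed. It says nothing about conception later, over the four to six three-weekly cycles of chemotherapy. A centre applying item q exactly as written could therefore randomise a fertile woman with no contraceptive requirement placed on her, and record her correctly as eligible. What is at stake is the safety of that patient and of a possible pregnancy.

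**Working it through.** The plan gives no figure on this point, so the check is one of logic, followed by a search for any other rule that would close the gap.

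**Step 1. Define the conditions.** A = not pregnant. B = no child-bearing potential. C = adequate contraception in use. Item q as written is *A or B or C*. The meaning suggested by the sentence on men is *A and (B or C)*.

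**Step 2. List the possible patients.** A woman without child-bearing potential cannot be pregnant, so B implies A and six combinations remain.

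| A | B | C | As written: A or B or C | Apparent intent: A and (B or C) |
|---|---|---|---|---|
| yes | yes | yes | eligible | eligible |
| yes | yes | no | eligible | eligible |
| yes | no | yes | eligible | eligible |
| yes | no | no | **eligible** | **not eligible** |
| no | no | yes | eligible | not eligible |
| no | no | no | not eligible | not eligible |

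The two readings differ in the fourth and fifth rows. The fourth row is the practical one: a fertile, non-pregnant woman using no contraception. The fifth row is discussed under the objection.

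**Step 3. Look at what the 'or' does to the sentence.** Since B implies A, the written rule reduces to *A or C*. The clause on child-bearing potential then changes nobody's eligibility. Under *A and (B or C)* it does the work one would expect, because it exempts women who cannot conceive from the contraception requirement. A clause with no effect is a further sign that the connectives are wrong.

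**Step 4. Look for another rule.**

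- The opening line of Section 3.3.2 requires all lettered items to be met. It does not change how the alternatives inside item q combine.
- Items n (interfering illness or treatment), p (fitness for the regimens) and r (breastfeeding) do not mention contraception.
- The test in Section 3.3.1 can establish A at entry. It cannot establish C.
- Section 6.4 adds no repeat test.
- The record of changes lists an addition to the eligibility criteria, on liver function, but no correction to the contraception wording.

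No other section of the latest protocol shown to us requires contraception of women.

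**The case against.** The strongest reply is that item q should be read as a whole. *Also*, in the sentence on men, presupposes that fertile women are already expected to use contraception. A woman must satisfy the investigator, which leaves room for judgement. Item p requires fitness for the regimens, queries are to be raised before randomisation, and for telephone and fax entry the trials office goes through a checklist. Many investigators would probably apply the sensible meaning.

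Much of this stands, and it limits the point. Four stronger readings are tempting, and the documents do not support them:

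- **That the trial chose to protect women less than men.** The word *also* and the redundant clause both point to a slip in the connectives.
- **That a pregnant woman could enter by reporting contraception.** The fifth row of the table allows this formally, but the listed pregnancy test, the investigator's judgement and item p make it largely an artefact of logic.
- **That fertile women in the trial went without any contraception requirement.** The patient information and consent pages were removed before review, and the eligibility checklist (Form Pre-a, Section 6.5) is not shown. Either may carry contraception instructions. They would not alter the wording of item q, but they bear on its practical consequence.
- **That a period of exposure after the test can be calculated.** Section 3.3.1 gives the pregnancy test no time window, so the interval from test to first dose is unknown. The protocol also applies the word clastogenic only to etoposide and not to the combined treatment.

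What the reply does not remove is that the written rule yields the wrong answer for an identifiable patient. A multicentre, multi-country trial should not depend on each centre reading past the text.

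**Conclusion.** The point holds as a drafting fault in an eligibility rule. As written, item q admits a non-pregnant woman of child-bearing potential using no contraception, and this conflicts with the sentence beside it and with its evident intent.

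Its size cannot be given as a number. Entry is open to either sex from age 18, so fertile women are not excluded, but the documents do not say how many were expected. The number is probably small. The matter is one of participant safety and does not touch the sample size, power or primary analysis.

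The conclusion rests on the literal text of the latest protocol and on there being no overriding rule in the sections available. An instruction in the removed patient pages or in the checklist would lessen the practical consequence, but the protocol wording would still need correcting.

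**What to change.** Reconcile the two sentences of item q by correcting the connectives: a female patient must not be pregnant and, in addition, must either lack child-bearing potential or be using adequate contraception. Bring the corresponding line of the eligibility checklist (Form Pre-a) into agreement, since that is what is worked through at randomisation.

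Rewording "Pregnancy test (if applicable)" in Section 3.3.1 would add little, because for a pregnancy test applicable naturally means women who could be pregnant.

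The cost is one reworded sentence and one checklist line. The change remains an entry criterion. It does not by itself govern what happens later in treatment, and no dose, schedule or analysis is affected.

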### 3.4 RANDOMISATION

Randomisation will be administered centrally by the trials office at the Christie Hospital. This is a multi-centre randomized phase III trial. Patients will be randomized on a 1:1 basis to one of two treatment arms. The allocation method will be minimization with a random element. Randomisation will be implemented in a bespoke computer application at the randomisation centre. The factors controlled for in the allocation will be:

Institution  
Planned number of cycles (4 or 6)  
Performance status (0/1 or 2) {PS2 equivalent to KP 50, 60}

The arm that would result in less imbalance will be allocated with probability 0.75. There will be a 'burn-in' period of 20 cases in which allocation will be completely random.

Randomisation can only be performed **after** confirmation that the patient is eligible (including recording of LDH, sodium and alkaline phosphatase results) and that the patient has signed consent. The system used does not permit any editing of fields by users after arm allocation has been performed.

**[contact]**

**Randomisation by telephone:** The researcher calls the randomisation line and supplies a verbal password for the study. A checklist is checked over the telephone before randomisation. Randomisation will be performed using the computer system, callers will be advised of the patient's trial number and treatment allocation. Please record these on the eligibility checklist and return a copy to the trials office ([contact]). An e-mail confirmation will be sent to pre-arranged e-mail addresses for each centre.

**Randomisation by fax:** The randomization form must be completed, signed by an authorised member of staff and faxed to the fax randomisation line. On receipt of the fax staff at the trials office will check the eligibility checklist and perform the randomisation. An e-mail confirmation will be sent to pre-arranged e-mail addresses for that centre.

This trial is a comparison of treatment policies, once a patient has been randomised that patient remains in the trial and full documentation is always required. Inevitably some patients will stop treatment early, either because the patient does not wish to continue or because the responsible clinician feels it is not in the patient's best interest to continue. For patients who stop treatment early the responsible clinician should continue to complete as much clinical information as possible. As a minimum, follow-up data on progression and survival status should be returned regularly (unless explicit consent for this is withdrawn).

